# Study protocol of the GRoningen early-PD Ambroxol treatment (GREAT) trial: a randomized, double-blind, placebo-controlled, single center trial with ambroxol in Parkinson patients with a GBA mutation

**DOI:** 10.1186/s12883-024-03629-9

**Published:** 2024-05-01

**Keywords:** Ambroxol, Disease modifying therapy, GBA1, Glucocerebrosidase, Interventional study, Parkinson’s disease

## Abstract

**Background:**

To date, no disease modifying therapies are available for Parkinson’s disease (PD). Since PD is the second most prevalent neurodegenerative disorder, there is a high demand for such therapies. Both environmental and genetic risk factors play an important role in the etiology and progression of PD. The most common genetic risk factor for PD is a mutation in the *GBA1*(GBA)-gene, encoding the lysosomal enzyme glucocerebrosidase (GCase). The mucolytic ambroxol is a repurposed drug, which has shown the property to upregulate GCase activity in-vitro and in-vivo. Ambroxol therefore has the potency to become a disease modifying therapy in PD, which was the reason to design this randomized controlled trial with ambroxol in PD patients.

**Methods:**

This trial is a single-center, double-blind, randomized, placebo-controlled study, including 80 PD patients with a GBA mutation, receiving either ambroxol 1800 mg/day or placebo for 48 weeks. The primary outcome measure is the Unified Parkinson’s Disease Rating Scale motor subscore (part III) of the Movement Disorder Society (MDS-UPDRSIII) in the practically defined off-state at 60 weeks (after a 12-week washout period). Secondary outcomes include a 3,4-dihydroxy-6-18F-fluoro-I-phenylalanine ([^18^F]FDOPA) PET-scan of the brain, Magnetic Resonance Imaging (with resting state f-MRI and Diffusion Tensor Imaging), GCase activity, both intra- and extracellularly, sphingolipid profiles in plasma, Montreal Cognitive Assessment (MoCA), quality of life (QoL) measured by the Parkinson’s Disease Questionnaire (PDQ-39) and the Non-Motor Symptom Scale (NMSS) questionnaire.

**Discussion:**

Ambroxol up to 1200 mg/day has shown effects on human cerebrospinal fluid endpoints, which supports at least passage of the blood-brain-barrier. The dose titration in this trial up to 1800 mg/day will reveal if this dose level is safe and also effective in modifying the course of the disease.

**Trial registration:**

NCT05830396. Registration date: March 20, 2023.

**Supplementary Information:**

The online version contains supplementary material available at 10.1186/s12883-024-03629-9.

## Background

### GBA-PD

Parkinson’s disease (PD) is the second most prevalent neurodegenerative disease and is characterized by various motor- and non-motor problems [1, 2]. Currently, no disease-modifying therapies are available [3]. PD is a multifactorial disorder, with both environmental and genetic risk factors playing an important role in its etiology and progression [4]. The most common genetic risk factor for PD is a mutation in the *GBA1-*gene (GBA), encoding the lysosomal enzyme glucocerebrosidase (GCase) [5]. GCase is a lysosomal hydrolase enzyme responsible for the degradation of the sphingolipid (SL) glucosylceramide (GluCer) into ceramide and glucose. The GBA gene is primarily known for its role in Gaucher’s disease (GD), in which GluCer accumulates in visceral organs [6]. GD is caused by a homozygous variant in the GBA gene. In GD over 400 variants of the GBA gene have been reported. The heterozygous GBA variants will not cause GD, but have shown to increase the risk of developing PD, albeit with a relatively low penetrance [7]. GBA variants are classified according to their clinical manifestation in GD (mild, severe), or the risk they pose for developing PD. Some mutations do not cause GD in homozygous form, but do attribute to the risk for PD [8, 9]. These are referred to as risk variants. Additionally, there are variants of which the clinical significance is unknown. A large nation-wide screening in the Netherlands showed that 15% of the included PD patients carried a GBA mutation, compared to 6,4% in the control group [10]. This screening also showed that over 60% of all mutations are classified as risk variants. PD patients carrying GBA mutations (GBA-PD) tend to have a more severe and rapid progression of both motor and non-motor symptoms [11, 12]. This is not only true for the GD-associated mild and severe variants, but also for risk variants, although the influence of risk factors less clear at this moment [12, 13].

GBA mutations are directly related to loss of GCase activity and lysosomal dysfunction [14, 15]. The exact mechanism behind the reduction of GCase activity remains unclear, although several hypotheses have been formulated [16]. The most widely acknowledged theory concerns a reciprocal relationship between GCase activity and alpha-synuclein aggregation, which plays a central role in the development of PD [17–19]. Other studies, however, could not verify this [20, 21]. Further potential underlying mechanisms include endoplasmic reticulum (ER) stress [22, 23] and deregulation of the autophagic-lysosomal pathway [20, 24].

Reductions in GCase activity may also play a role in sporadic PD, as these individuals have low levels of GCase in the brain and cerebrospinal fluid (CSF) as well [25]. Upregulation of brain cytosolic and lysosomal GCase activity may reduce alpha-synuclein (aSyn) levels, mediating a neuroprotective effect in patients with PD, both with and without GBA mutations [25, 26].

Interestingly, mild GCase deficiencies in GBA-PD do not result in GluCer accumulation, so the lowering of GluCer is unlikely to produce a therapeutic benefit**.** Recent data show that plasma levels of GluCer in GBA-PD and idiopathic PD are similar [27]. Several other studies investigating GluCer levels in CSF and plasma of GBA-PD patients have confirmed that these levels are not increased significantly [28–30]. Moreover, GluCer levels are not elevated in GBA-PD brain tissue [31, 32]. So, GCase mutants have an increased risk of developing PD and may progress more quickly, but this does not seem to be the consequence of an increase in GluCer.

Alternative explanations are related to the fact that GCase plays a role in a complex recycling pathway of SLs, involving various other SLs, besides GluCer. Possibly, mutant GCase has a more widespread effect on this pathway, with a central role for cytosolic ceramide [33]. This cascade is pivotal in the adaptation and reparation of (intra)cellular membranes, involved in synapse formation, neurotransmitter release and autophagy, among others [34]. Therefore, insight into behavior of the SLs involved in this pathway might be of key importance to understand the pathophysiology of GBA-related PD.

### Ambroxol

Ambroxol is a mucolytic expectorant and available on the market in more than 50 countries for over 30 years [35]. Ambroxol acts as a chaperone for GCase, allowing effective trafficking, from the ER and Golgi system to the lysosome [36]. Importantly, ambroxol can be administered orally and crosses the blood-brain barrier [37]. Oral ambroxol has also been demonstrated to increase GCase levels in non-human primates, as well in humans [38–40]. These results support the potential for using ambroxol as a disease-modifying treatment for synucleinopathies, like PD. Studies with ambroxol in humans so far showed that ambroxol can be safely given in those higher dosages for a longer period [39, 41, 42]. Asymptomatic mild proteinuria and increased respiratory mucus production were the only major related adverse reactions [41].

### Dose selection

Participants in this study will receive a maximal dose of 1800 mg/day, using 600 mg capsules, which are titrated with 600 mg per week, up to 1800 mg/day after 3 weeks, if tolerated. This maximal dose was based on previous pharmacological data on ambroxol in humans. One study with PD patients used doses of 1260 mg/day without any serious adverse events [39]. Additionally, a meta-analysis showed that doses of ambroxol up to 30 mg/kg/day to treat pneumonia, were also tolerated very well [43]. Ambroxol has also been administered intravenously in doses up to 20 mg/kg/day, which did not show any adverse events (AEs) [44]. A study in children with oral ambroxol 40 mg/kg/day for 10 days also did not show any AEs. So, the safety profile of ambroxol, even in higher doses, seems to be good.

## Methods/design

### Trial design

This study is a randomized, placebo-controlled trial with ambroxol in non-demented PD patients with a proven GBA mutation. This study is reported following the SPIRIT guidelines (see Supplementary file 1) [45].

This is a single-center trial carried out in the University Medical Center Groningen, with ambroxol versus placebo during 48 weeks, followed by an open 12-week washout period, creating an overall duration of 60 weeks. During these 48 weeks, patients will receive either ambroxol 1800 mg/day or placebo. This includes a 3 week titration period, in which the dose will be increased with 600 mg/day every week. The primary endpoint is the change in off-period scores of the Unified Parkinson’s Disease Rating Scale of the Movement Disorder Society (MDS-UPDRS) part III between baseline and 60 weeks, including a 12-week wash-out period, to exclude an unlikely therapeutic effect of ambroxol. Secondary endpoints are also compared between baseline and 60 weeks, and include safety/tolerability of ambroxol, change in GCase activity in monocytes, striatal F-DOPA uptake as measured by [18]F-DOPA PET scans of the brain, resting state fMRI, related to structural MRI and diffusion tensor imaging (DTI) tractography, quality of life (QoL), measured by the Parkinson’s Disease Questionnaire-39 (PDQ-39), the presence and severity of non-motor symptoms using the Non-Motor Symptoms Scale (NMSS), cognitive changes measured by the MOCA and finally the changes in Levodopa equivalent doses (LED). For an overview of study visits, see Fig. 1.

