### Interventions

The ambroxol capsules of 600 mg were produced exclusively for this study by a Dutch pharma company. Patients will be titrated up to ambroxol 1800 mg/day or placebo (one capsule three times a day) in 3 weeks, starting with 600 mg once daily during the first week, with weekly increases of 600 mg/day. The dosages of the individual subjects will be decreased if serious side effects occur that are probably related to the treatment.

At 48 weeks, all patients stop using either ambroxol or placebo, followed by a 12 week washout period. This washout period ensures the absence of any symptomatic effect of ambroxol.

At 60 weeks, all baseline measurements will be repeated. Participants will continue their regular medication regimen during the study. Dose adaptations of their standard regimens will be allowed, and will be analyzed post-hoc.

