### Outcomes

The primary endpoint of this study is the change in the MDS-UPDRS part III motor subscale in the practically defined OFF medication state between baseline and 60 weeks. The MDS-UPDRS part III is a motor scale using a score range from 0 to 132 points, with 0 indicating no disability and 132 indicating total disability. All 18 items are evaluated on a five-point scale from 0 to 4. All items contain clearly formulated instructions for both the patient and the investigator [46, 48]. MDS-UPDRS part III in OFF medication state will be assessed every 12 weeks. OFF medication state is defined as withdrawal from dopaminergic medication for at least 8 hours. To ensure the reliability of the UPDRS III scores, several measures were implemented. First, all examiners had to pass the formal MDS-UPDRS training. All MDS-UPDRS III assessments are video recorded and scored by or together with the main co-investigator.

The study has several secondary endpoints, which are also comparing data at 60 weeks versus baseline scores. The following secondary endpoints will be assessed during this study.

*[*
^*18*^
*F]F-DOPA PET*

The PET tracer [^18^F]F-DOPA PET binds to aromatic amino acid decarboxylase (AADC) and estimates the rate of decarboxylation of [^18^F]F-DOPA to [^18^F]fluorodopamine which corresponds to striatal dopamine production and is considered a reliable tool to assess nigrostriatal dopamine synthesis capacity in vivo [49]. The PET-scan is performed after at least 6 hours of fasting (4 hours for diabetic patients). Participants are premedicated with carbidopa, 60 minutes before receiving 200 MBq of the F-DOPA tracer. The F-DOPA PET scan is performed 90 minutes after injection of the tracer on a Siemens HR+ camera. [^18^F]F-DOPA PET will be performed at baseline and at 60 weeks, to analyze the change in striatal activity. [^18^F]FDOPA striatal-to-occipital ratios of the putamen and caudate nucleus will be calculated to quantify the striatal dopaminergic innervation.

*MRI*

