A structural MRI will be performed, which will also serve as the template for PET analysis. In addition, resting state f-MRI will be performed. Fluctuations in the BOLD signal will be used to investigate the functional architecture and connectivity within the brain. Variations in the nigrostriatal projections between the ambroxol and placebo groups will be analyzed using diffusion tensor imaging (DTI) MRI. The microstructural degradation of the nigrostriatal tract in PD patients is associated with the severity of motor symptoms [50]. All MRI sequences will be performed at baseline and 60 weeks.

*GCase activity and SL measurements in mononuclear cells and blood plasma*

The GBA gene encodes the lysosomal enzyme GCase, which catalyzes the hydrolysis of the SL GluCer to produce ceramide. Progression-related single allele mutations are associated with a mild (up to 50%) loss of GCase activity [51]. However, the GluCer levels of PD patients with and without GCase did not show significant differences [27, 30, 31].

So, there are still many questions to be answered about the relationship between lower GCase activity and faster disease progression [52]. Reduced GCase activity may not be related to absolute changes of SLs, but to a reduced flux (the amount of SL recycled per time) through the SL recycling pathway [33]. The recycling SL pathways are required to maintain the availability of cytosolic ceramide, which is needed to adapt and/or repair all kinds of lipid-bilayer membranes in the cell [53]. Unfortunately, measurements of the SL flux are very complex and expensive, and still need validation. Alternatively, static SL levels might give a valuable insight in the effect of ambroxol on the recycling pathway. However, recent data on the biomarker profile of SL in GBA vs non-GBA PD patients did not show any correlation between static intra- and extracellular SL levels. Moreover, only plasma measurements of SL showed differences between GBA-PD, idiopathic PD and healthy volunteers. At the same time, plasma measurements of SL showed the lowest intra-patient variability [54]. Therefore, we choose to perform only static SL measurements in plasma, including all pivotal pathways related to the formation or breakdown of ceramide.

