Additionally, the effect of ambroxol on the enzymatic activity of GCase will be measured. GCase activity will be quantified in peripheral blood mononuclear cells (PBMCs), using 5-(Pentafluorobenzoylamino) Fluorescein Di-beta-D-Glucopyranoside (PFB-FDGlu) [55].

The following sphingolipids will be measured (isomers):Ceramide (d18:1/18:0)Glucosylceramide (d18:1/18:0)Galactosylceramide (d18:1/18:0)Sphingomyelin (d18:1/18:0)Dihydroceramide (d18:1/18:0)Ceramide-1-phosphate (d18:1/18:0)Sphingosine (d18:1)Sphingosine-1-phosphate (d18:1)

Figure 2 shows a schematic overview of part of the SL pathway and the specific measurements performed. Measurements will take place at baseline and after 12, 48 and 60 weeks.

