### Statistical analyses

All statistical tests will use an alpha of 0.05, with two-way testing. Data will be analyzed according to the intention-to-treat principle, which will include all patients having completed at least 1 post-randomization follow-up visit. A summary of baseline characteristics and the outcomes at baseline at subsequent treatment-phase visits for the whole cohort will be presented as point estimates with their standard deviations, or as counts and percentages where the data are categorical. Baseline characteristics will be summarized per randomization group.

Primary outcome analyses will evaluate the impact of treatment allocation (ambroxol or placebo) on the difference between MDS UPDRS part III OFF medication scores at 60 weeks follow up. A regression analysis of covariance (ANCOVA) approach will be used to analyze the effect of ambroxol. This is done to adjust for stratification factors and baseline MDS-UPDRS part III values. Also, post-hoc analysis will determine eventual effects of changes in LED on the primary outcome.

Secondary continuous outcomes will be analyzed using regression analyses as well, also adjusting for stratification factors and baseline scores. Comparison of adverse events between treatment groups will be done with χ^2^ tests.

Post-hoc analysis will be performed to correlate GCase activity at baseline and at 60 weeks with MDS-UPDRS III scores. Additionally, the effect of ambroxol on pathological (i.e. severe and mild) GBA variants specifically will be analyzed post-hoc.

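### GCase activity and sphingolipids are compared at week 60, 12 weeks off drug, and no between-arm analysis is stated for the on-drug samples at weeks 12 and 48

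*Protocol article*

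**What the plan says.** The comparison time point is given twice. Trial design states: "Secondary endpoints are also compared between baseline and 60 weeks, and include safety/tolerability of ambroxol, change in GCase activity in monocytes". Outcomes repeats it for all secondary endpoints: "The study has several secondary endpoints, which are also comparing data at 60 weeks versus baseline scores". The list that follows that sentence contains the item on GCase activity and sphingolipids.

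Dosing has ended by then. Interventions says: "At 48 weeks, all patients stop using either ambroxol or placebo, followed by a 12 week washout period".

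The purpose of the two biochemical measures is also given under Outcomes. For the enzyme: "Additionally, the effect of ambroxol on the enzymatic activity of GCase will be measured". For sphingolipids: "static SL levels might give a valuable insight in the effect of ambroxol on the recycling pathway". The sampling schedule is wider than the comparison: "Measurements will take place at baseline and after 12, 48 and 60 weeks".

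Statistical analyses plans regression for continuous secondary outcomes, adjusted for baseline and the stratification factors, without naming a visit. It also plans a descriptive summary of treatment-phase visits for the cohort as a whole. The only analysis there that names GCase is this one: "Post-hoc analysis will be performed to correlate GCase activity at baseline and at 60 weeks with MDS-UPDRS III scores".

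**The concern.** A washout before the final assessment suits the motor endpoint, because the trial wants a difference that outlasts any short-term benefit of the drug. The same rule has been carried over to a direct biochemical marker of drug action. There the question is what happens while the drug is being taken, and week 60 is the one post-baseline sample taken without it.

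What is at stake is interpretation. If GCase shows no difference at week 60, the reader cannot tell whether ambroxol failed to raise GCase or raised it and the rise faded. If the motor endpoint is also null, the trial would be poorly placed to say whether the drug failed to act on the enzyme or acted without clinical benefit. The planned correlation has the same limit: both of its GCase values are taken off drug, so it says little about treatment-induced change if the effect has reversed.

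**Working it through.** **1. Timing.** Dosing ends at week 48 and the comparison is at week 60: 60 − 48 = 12 weeks off drug.

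| Sample | On drug? | Stated between-arm comparison | In the GCase–motor correlation |
|---|---|---|---|
| Baseline | no | reference | yes |
| Week 12 | yes | none | no |
| Week 48 | yes (end of dosing) | none | no |
| Week 60 | no | yes | yes |

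Two of the three post-baseline samples are on drug. Neither has a stated comparison between arms. The whole-cohort summary pools the arms, so it cannot show a treatment effect.

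**2. The plan's own figure.** The only computed design figure is the sample size for the primary endpoint. Inputs from Sample size and power calculation: difference 3.91, SD 6.1, two-sided 5%, power 80%. Equal allocation is my assumption, because no ratio is stated.

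n per arm = 2 × (1.960 + 0.842)² × 6.1² / 3.91² = 38.2, rounded up to 39, or 78 in total. The t-test version gives 39.2, rounded up to 40, or 80 in total, with power 0.81. The stated 80 reproduces and is not in question. I use 40 per arm below.

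**3. What the week-60 visit could cost (illustration).** The documents give no GCase effect, SD or reversal rate, so these are assumptions shown over a range. Let d be the on-drug standardised difference between arms and r the fraction left at week 60. Power is that of a two-sample t-test with non-centrality d × r × √(40/2) and 78 degrees of freedom. It ignores dropout and any gain from baseline adjustment.

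| d on drug | r = 100% | 50% | 25% | 10% | 0% |
|---|---|---|---|---|---|
| 0.64 | 81% | 29% | 11% | 6% | 5% |
| 1.0 | 99% | 60% | 20% | 7% | 5% |
| 1.5 | >99% | 91% | 38% | 10% | 5% |

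The value 0.64 is the primary endpoint's 3.91/6.1, used only as an anchor. At r = 0 the test has only its 5% false-positive rate, whatever the on-drug effect.

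**4. How r depends on the speed of reversal.** If the effect decays exponentially with half-life h weeks, r = 0.5^(12/h): about 0.02% for h = 1, 1.6% for h = 2, 12.5% for h = 4 and 50% for h = 12. Nothing in the documents selects among these values.

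**The case against.** The strongest reply is that the documents never say the biochemical effect is gone by week 60. The stated role of the washout is narrower: "This washout period ensures the absence of any symptomatic effect of ambroxol". Ambroxol is described as a chaperone for GCase, but no duration of action is given. A reader might infer that the week-60 contrast must be near zero even if the drug works fully on the enzyme. The documents do not support that: it is one end of an unknown range, and a persistent effect would still be visible. This part of the objection stands, and the point is worded conditionally for that reason.

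A second reply is that the on-drug samples are not simply discarded. The summary of treatment-phase visits is a stated use, and the regression sentence names no visit, so an on-drug analysis may be intended and set out elsewhere. It is therefore fair to say only that no between-arm analysis is stated for those visits. But the article does more than stay silent: it states week 60 as the comparison in two places. A week-48 analysis in another document would have to be reconciled with that.

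Third, the Trial design sentence is loose. It lists safety under the same baseline-to-week-60 rule, although adverse events are followed throughout. It also names GCase but not sphingolipids. Both remarks are true. The general sentence in Outcomes nevertheless covers both measures, and the correlation names baseline and week 60 explicitly.

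Finally, GCase is measured in blood cells and sphingolipids in plasma, and the Discussion itself calls in-vivo GCase measurement debated. A reader might infer that a week-48 contrast would settle whether the drug reached its target in the brain. It would not. It would answer the peripheral question that the protocol says it is asking.

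**Conclusion.** The point holds as a stated rule that fits its own purpose poorly. The week-60 comparison is explicit, the purpose is the effect of ambroxol on GCase and the sphingolipid pathway, and the samples better suited to that purpose are already scheduled.

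The size of the loss is unknown and ranges from none (effect fully persistent) to complete (effect fully reversed). In the illustration with d = 1.0, that is power between 99% and 5%. These figures rest on assumed effect sizes, an assumed equal split of 80 patients and an assumed residual fraction. The timing mismatch rests on none of them.

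This is a free improvement to secondary endpoints. It is not a flaw that threatens the trial: the primary endpoint, its sample size and the randomisation are unaffected, and the data needed for the better analysis are due to be collected.

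**What to change.** Before unblinding:

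- Name the between-arm difference at week 48 as the main contrast for GCase activity and for sphingolipids, with week 12 in support, adjusted for baseline and the stratification factors.
- Keep week 60 for both measures, labelled as a measure of persistence after stopping.
- Correlate the on-treatment change in GCase (baseline to weeks 12 and 48) with the change in MDS-UPDRS III from baseline to week 60, adjusted for arm. The existing baseline and week-60 correlation can stay as a descriptive addition.
- Amend the general statements in Trial design and Outcomes so that week 60 is no longer given as the comparison for every secondary endpoint.

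The cost is wording and analysis time. No extra patients, visits or samples are needed.
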